### 10.2 Subject Registration

- Written informed consent must be obtained before any study specific medical procedures are performed.
- All patients must be registered with the UC Davis Cancer Center.
- Subjects being enrolled during the study will need to be assigned a dose level for treatment (see section 7.1).

### 10.3 Baseline Screening

- To be completed within 6 weeks of registration:  
CT of Chest, MRI/CT of primary tumor location
- To be completed within 4 weeks of registration:  
History & Physical, including vitals, PS  
EKG  
Labs
- To be completed within 1 week of registration:  
Serum or urine pregnancy test

### 10.4 Study Visits

See study calendar (section 10.1)

#### 10.4.1 Toxicities and Adverse Events

Toxicities and adverse events will be assessed at each visit using the NCI Common Toxicity Criteria for Adverse Events v3.0 (<http://ctep.cancer.gov/reporting/ctc.html>). **Acute and long-term radiation toxicity must be graded at each visit for the following CTCAE categories:**

- 1) Dermatologic/Rash: Dermatitis associated with radiation**
- 2) Musculoskeletal/Soft Tissue: Extremity (as appropriate for location of tumor)**
- 3) Musculoskeletal/Soft Tissue: Fibrosis—deep connective tissue**

#### 10.4.2 Assessment of Wound Complications

An accurate assessment of post-operative wound complications is vital for the accurate reporting of toxicity associated with this regimen. Major wound complications will be defined as described by O'Sullivan et al. in the randomized, controlled trial of preoperative versus postoperative radiation in the treatment of STS of the extremities.

**A major wound complication is defined as a secondary operation under general or regional anesthesia for wound repair (debridement, operative drainage, and secondary wound closure including rotationplasty, free flaps, or skin grafts), or wound management without secondary operation. Wound management includes an invasive procedure without general or regional anesthesia (such as aspiration of seroma), readmission for wound care such as intravenous antibiotics, or persistent deep packing for 120 days or longer.**

### 10.4.3 Follow-up

Follow-up for all patients registered on this study, including those who do not receive any protocol therapy, will be required for 5 years following completion of therapy. Follow-up after completion of protocol therapy will be limited to monitoring for 1) development of local tumor recurrence, 2) development of distant metastatic disease, 3) survival, and 4) late toxicity, including limb function impairment and secondary malignancy. Follow-up reports are due every 4 months.

### 10.4.4 Schedule of Events

|                                               | Prior to
Registration | Prior to Day 1
of Treatment | Time of Pre-
Surgical
Restaging* | Post
Treatment
Follow-up |
|-----------------------------------------------|--------------------------|--------------------------------|----------------------------------------|--------------------------------|
| Tests & Observations        |                          |                                |                                        |                                |
| History and Progress Notes                    | X                        | X                              | X                                      | X                              |
| Physical Examination                          | X                        | X                              | X                                      | X                              |
| Pulse, Blood Pressure**                       | X                        | X                              | X                                      | X                              |
| Height/Weight                                 | X                        |                                |                                        |                                |
| Performance Status                            | X                        | X                              | X                                      | X                              |
| Treatment Toxicity
Assessment              |                          | #                              | #                                      | #                              |
| Pathology Review                              | ##                       |                                | ##                                     |                                |
| Laboratory Studies              |                          |                                |                                        |                                |
| CBC, Differential, Platelets                  | X                        |                                | X                                      | PRN                            |
| Serum Chemistries***                          | X                        |                                | X                                      | PRN                            |
| Pregnancy Test****                            | X                        |                                |                                        |                                |
| INR                                           | X                        | ###                            | ###                                    |                                |
| EKG                                           | X                        |                                |                                        | PRN                            |
| DCE-MRI                                       |                          | See section 9.1                | See section 9.1                        |                                |
| Tumor tissue/serum for
correlative studies |                          | See section 9.2                | See section 9.2                        |                                |

### **Staging**

|                           |   |  |   |      |
|---------------------------|---|--|---|------|
| Chest CT                  | X |  | X | #### |
| MRI or CT of primary site |   |  |   | #### |

\* After completion of combined sorafenib/radiotherapy and within 4 weeks of surgery.

\*\* Blood pressure to be monitored weekly during treatment and study period until time of surgery.

\*\*\* Comprehensive metabolic panel (including BUN, creatinine, bilirubin, AST, ALT, alkaline phosphatase).

\*\*\*\* For women of childbearing potential.

# Toxicity assessments per CTCAE v 3.0 (See section 11.4.1 and appendix B). Long term follow-up for radiation toxicity and limb function required per section 11.4.1.

- ## Initial diagnostic pathology specimen must be submitted for central review. Post-resection specimen will be carefully evaluated for percent tumor necrosis following preoperative treatment (see section 7.5).
- ### INR should be closely monitored for patients receiving warfarin. INR does not need to be monitored during study for patients not receiving warfarin.
- #### Post-treatment imaging studies for disease recurrence is at investigator's discretion. It is suggested that a chest CT or chest X-ray be performed every 4 months for the first 2 years, every 6 months for the 3rd year, and yearly for the 4th and 5th year. It is suggested that MRI or CT of the primary site be obtained yearly for the first 3 years.

### 10.5 Specimen Submission for Molecular Correlative Studies

With the patient's consent, tissue and blood specimens will be submitted as outlined below.

- Paraffin-embedded tissue blocks or slides from the time of diagnosis (prior to therapy) and at the time of surgical resection will be submitted for expression of relevant molecular targets. 1-2 paraffin-embedded tissue blocks containing formalin-fixed tumor tissue should be submitted for evaluation and expression of mutations in relevant molecular pathways. Paraffin blocks should be processed according to standard institutional protocols. If blocks are unavailable, 16 unstained slides are acceptable alternatives.
- Two blood specimens will be collected from each patient prior to treatment (2 x 10 mL). Subsequent blood specimens (1 x 10 mL) will be collected at selected intervals as indicated in the study calendar (see section 10.1, weeks 2, 6, 9, and end of study). In the event that a patient is removed from the study, a blood specimen (approximately 10 mL) will be obtained at the time the patient is removed from protocol treatment.

One blood specimen should be collected in a 10 mL purple-top (EDTA) tube, inverted several times, and placed on wet ice until centrifugation. The tube should be centrifuged as soon as possible at approximately 1,000 to 1,500 rpm for 10 minutes. Plasma should be removed and placed in 1 mL aliquots in labeled cryotubes. Buffy coat cells should be separately removed and placed in labeled cryotubes. All specimens must be labeled with protocol number, patient registration number, and date of specimen collection. All tubes are then to be frozen (snap frozen with liquid nitrogen if possible) and stored at -70°C until shipped to the laboratory on dry ice as detailed below.

The second blood specimen should be collected in a 10 mL red-top tube, allowed to clot at room temperature for 30 minutes, and placed on wet ice until centrifugation. The tube should be centrifuged at 3000 rpm for 10 minutes. Serum should be removed and placed in 1 mL aliquots in labeled cryotubes. All specimens must be labeled with protocol number, patient registration number, and date of specimen collection. All tubes are then to be frozen (snap frozen with liquid nitrogen if possible) and stored at -70°C until shipped to the laboratory on dry ice as detailed below.

- Shipping instructions: All archival paraffin block or slide specimens should be sent at ambient temperature. Frozen specimens should be shipped on dry ice. These should be shipped by overnight courier Monday through Wednesday only, to the following address:

[name]  
[name], Division of Hematology/Oncology  
UC Davis Cancer Center  
[name]  
[name]

[figure not shown]

A Specimen Submission Form must be submitted with each specimen. Institutions should notify the recipient by either phone or fax prior to shipping specimens. This will allow the recipient to track the package in the event that there are any problems in delivery.

The Federal Guidelines for Shipment are as follows (these periodically change, please check for the most current guidelines):

1. The specimen must be wrapped in an absorbable material
2. The specimen must then be placed in an AIRTIGHT container (resealable bag)
3. Pack the resealable bag and specimen in a styrofoam shipping container
4. Pack the styrofoam shipping container in a cardboard box
5. The cardboard box should be labeled “UN3373 Biological Substance, Category B “BIOHAZARD”

## 11.0 MEASUREMENT OF EFFECT

### 11.1 Pathologic Response

This is the primary endpoint of the phase II trial. **(see section 7.5 for protocol-based determination of this endpoint)**

### 11.2 Radiographic and Clinical Response

The radiographic and/or clinical response of the primary tumor to preoperative therapy will be evaluated. The primary lesion will serve as the sole target lesion and will be recorded and measured at baseline. The longest diameter (LD) of the target lesion will be measured and reported as the baseline LD. The baseline LD will be used as reference to further characterize the objective tumor response of the measurable dimension of the disease.

Response and progression will be evaluated in this study using the new international criteria proposed by the Response Evaluation Criteria in Solid Tumors

(RECIST) Committee. Changes in only the largest diameter (unidimensional measurement) of the tumor lesions are used in the RECIST criteria.

### 11.3 Response Criteria

#### 11.3.1 Evaluation of target lesion

|                           |                                                                                                                                                                                          |
|---------------------------|------------------------------------------------------------------------------------------------------------------------------------------------------------------------------------------|
| Complete Response (CR):   | Disappearance of target lesion                                                                                                                                                           |
| Partial Response (PR):    | At least a 30% decrease in the sum of the longest diameter (LD) of target lesion, taking as reference the baseline sum LD                                                                |
| Progressive Disease (PD): | At least a 20% increase in the sum of the LD of target lesion, taking as reference the smallest sum LD recorded since the treatment started or the appearance of one or more new lesions |
| Stable Disease (SD):      | Neither sufficient shrinkage to qualify for PR nor sufficient increase to qualify for PD, taking as reference the smallest sum LD since the treatment started                            |

#### 11.3.2 Evaluation of best overall response

The best overall response is the best response achieved prior to surgical resection of the target lesion.

| Target Lesions | New Lesions | Overall Response |
|----------------|-------------|------------------|
| CR             | No          | CR               |
| PR             | No          | PR               |
| SD             | No          | SD               |
| PD             | Yes or No   | PD               |
| Any            | Yes         | PD               |

NOTE: In some circumstances, it may be difficult to distinguish residual disease from normal tissue. When the evaluation of complete response depends upon this determination, this will be determined at the time of surgical resection.

## 11.4 Time-to-Event Measures

### 11.4.1 Time to Local Recurrence

Defined as the duration of time from surgical resection of the primary tumor until local recurrence (amputated patients excluded).

### 11.4.2 Local Disease-Free Survival

Defined as the duration of time from surgical resection of the primary tumor until local recurrence or death, whichever occurs first.

### 11.4.3 Distant Disease-Free Survival

Defined as the duration of time from registration until development of distant metastatic disease or death, whichever occurs first.

### 11.4.4 Disease-Free Survival

Defined as the duration of time from surgical resection to local recurrence, distant metastatic disease, or death, whichever occurs first.

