#### 3.2 Secondary Objectives

- Phase I and II
  1. To describe the toxicities associated with neoadjuvant conformal RT in combination with sorafenib.
  2. To determine the rate of R0 (negative resection margin), R1 (microscopically positive resection margin), and R2 (macroscopically resection margin) following neoadjuvant conformal radiotherapy in combination with sorafenib.
  3. To determine the radiographic response rate to combined neoadjuvant conformal radiotherapy and sorafenib as defined by conventional RECIST criteria (**see section 11.3 for definition of RECIST criteria**).
  4. To obtain preliminary data regarding local disease control, distant disease control, progression-free survival, and overall survival with this novel therapeutic regimen.
  5. To assess functional and quality of life outcomes before, during, and after therapy using the established metrics including the Toronto Extremity Salvage Score (appendix 14.1.3) and the SF36 Health Survey (appendix 14.1.4)
- Phase II only
  1. To initiate analyses of molecular markers of tumor response assessment comparing (1) a microarray of a panel of serum angiogenic markers pre- and post-treatment; and (2) immunohistochemistry of tumor tissue pre- and post-treatment for expression of angiogenic proteins (VEGF, VEGFR1-3), growth factors correlated with hypoxia and resistance to radiation (EGF, FGF, HIF-1 $\alpha$ ), and modulators of proliferation and signal transduction (Ki-67, pERK).
  2. To analyze changes in tumor blood flow, blood volume, capillary permeability, and cell viability pre- and post-treatment with combined sorafenib/RT using dynamic contrast-enhanced MRI. The primary

endpoints of these studies will be the transfer constant (Ktrans) and the initial area under the gadolinium concentration time curve (IAUGC, mMgDomin—see section 9.1 for DCE-MRI imaging protocol).

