## 6.0 PATIENT ELIGIBILITY

### 6.1 Inclusion Criteria

1. Histologically confirmed soft-tissue sarcoma located on the extremity.
  - a. Intermediate or High grade (NCI grade 2 or 3/3-tier system),  $> 5$  cm in maximal dimension.
  - b. Low grade (NCI grade 1/3-tier system),  $> 8$  cm in maximal dimension.
  - c. No evidence of regional or distant metastatic disease.
2. Patient must be 18 years of age or older.
3. Patient must have an ECOG performance status of  $\leq 2$ .
4. Patient must have adequate bone marrow, liver, and renal function as assessed by the following:
  - a. Hemoglobin  $\geq 8.5$  g/dl
  - b. Absolute neutrophil count (ANC)  $\geq 1,500/\text{mm}^3$
  - c. Platelets  $\geq 100,000/\text{mm}^3$ .
  - d. Total bilirubin  $\leq 1.5$  mg/dL. NOTE: Patients with elevated bilirubin secondary to Gilbert's syndrome are eligible to participate in the study.
  - e. AST and ALT  $\leq 2.5$  times the institution upper limit of normal (ULN).
  - f. Creatinine  $\leq 1.5$  times ULN.
5. Females of childbearing potential must have a negative serum or urine pregnancy test within 7 days prior to the start of treatment . NOTE: Postmenopausal women must be amenorrheic for at least 12 months to be deemed not of reproductive potential.
6. Women of childbearing potential and men must agree to use adequate contraception (barrier method of birth control) prior to study entry and for

the duration of study participation. Men should use adequate birth control for at least three months after the last administration of sorafenib.

7. Ability to understand and the willingness to sign a written informed consent. A signed informed consent must be obtained prior to any study specific procedures.
8. INR < 1.5 or a PT/PTT within normal limits. Patients receiving anti-coagulation treatment with an agent such as warfarin or heparin **may** be allowed to participate. For patients on warfarin, the INR should be measured prior to initiation of sorafenib and monitored at least weekly, or as defined by the local standard of care, until INR is stable.
9. If patient is a cancer survivor, ALL of the following criteria must apply:
  - a. Patient has undergone potentially curative therapy for all prior malignancies.

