Resectability will depend upon the judgment of the operating surgeon. For the extremities, resection must be limb salvage procedure. Extremity patients who are not resectable without amputation may be amputated. Unresectable tumors may be palliated with surgery, chemotherapy, or additional radiation therapy. These patients will be taken off protocol.

**Note that documentation of wound complications is an integral part of this clinical trial. Wound complications are defined in section 10.4.2 and must be accurately recorded and reported.**

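### Disease-free survival does not count an isolated regional (nodal) recurrence and follow-up does not collect it, so DFS can be overstated

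*Protocol*

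**What the plan says.** Protocol 11.4.4 defines DFS in one sentence: "Defined as the duration of time from surgical resection to local recurrence, distant metastatic disease, or death, whichever occurs first". Three event types are named, and regional recurrence is not one of them.

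The eligibility criteria treat regional disease as a category of its own. Section 6.1 no. 1c requires: "No evidence of regional or distant metastatic disease".

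Section 10.4.3 restricts data collection after protocol therapy. Follow-up is "limited to monitoring for 1) development of local tumor recurrence, 2) development of distant metastatic disease, 3) survival", with late toxicity as the fourth item. Regional recurrence is not listed. The imaging suggested in the footnote to 10.4.4 covers the chest and the primary site and is left to the investigator.

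Section 13.2.4 plans Kaplan-Meier estimates and takes its definitions from 11.4. Section 13.2.3 plans exploratory Cox regression for time-to-event outcomes without naming which ones.

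**The concern.** A composite endpoint of freedom from disease should account for every way in which the disease can return. Here the protocol recognises three sites of disease (local, regional, distant) at entry but only two at failure. A patient who recurs in a regional node and nowhere else remains event-free in DFS under the literal definition.

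The follow-up restriction makes this more than a drafting slip. An analysis plan can redefine an event from data that were collected, but it cannot recover an event type that the follow-up reports never asked for.

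At stake is a descriptive estimate from a small single-arm trial. DFS is part of the hypothesis in the synopsis and would naturally be compared with historical results. The literal rule would tilt that comparison in one direction only.

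**Working it through.** The protocol gives no DFS rate, event count or power for DFS, so there is no figure to reproduce. The check has two parts.

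**1. The definitions side by side**

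| Place | Local | Regional | Distant | Death |
|---|---|---|---|---|
| Eligibility, 6.1 no. 1c | not applicable (primary tumor) | named | named | not applicable |
| DFS, 11.4.4 | event | not named | event | event |
| Follow-up list, 10.4.3 | collected | not named | collected | collected |
| Progression-free survival (PFS), 11.4.5 | event | not named, but may enter as progressive disease | event | event |

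The PFS entry rests on 11.3.1, where progressive disease includes the appearance of new lesions, and on 11.3.2, where any new lesion gives progressive disease. Those sections are written around response before surgery, so PFS may capture a later nodal lesion but does not clearly do so.

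**2. How much one missed event can matter**

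Inputs: 25 patients in phase II, and 30 to 35 in total (section 4.0). Objective 3.2 no. 4 covers both phases, so both denominators are shown. Assumptions: all n patients are resected, nobody is censored before the landmark time, and the nodal failure is not followed by a counted event before that time.

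The Kaplan-Meier estimate at a landmark is then (n − events)/n, so k missed events raise it by k/n:

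| Missed events | n = 25 | n = 30 | n = 35 |
|---|---|---|---|
| 0 | 0 | 0 | 0 |
| 1 | 1/25 = 4.0 points | 1/30 = 3.3 | 1/35 = 2.9 |
| 2 | 2/25 = 8.0 | 2/30 = 6.7 | 2/35 = 5.7 |

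The documents give no frequency p of isolated nodal failure, so p has to be assumed. The chance of at least one such patient is 1 − (1 − p)^n:

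| Assumed p | Expected number, n = 25 | At least one, n = 25 | At least one, n = 35 |
|---|---|---|---|
| 1% | 0.25 | 22% | 30% |
| 2% | 0.50 | 40% | 51% |
| 5% | 1.25 | 72% | 83% |
| 10% | 2.50 | 93% | 97% |

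Across this assumed range, the expected number of affected patients among 25 runs from well under one to between two and three.

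**The case against.** The strongest reply is that little rests on DFS. It is not among the objectives: 3.2 no. 4 and 13.2.4 name local control, distant control, PFS and overall survival. No test, power statement or decision uses it, and the Cox models in 13.2.3 are exploratory and do not name DFS. PFS, which is an objective, may already count a new nodal lesion as progressive disease. All of this stands and limits the importance of the point.

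A second reply is that a nodal failure may be followed by distant disease or death. The DFS event is then delayed rather than lost, and a later landmark is unaffected. That also stands, and it makes the per-patient figures upper limits.

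A third reply is that an assessor could record nodal disease under distant metastasis. That is possible, but the protocol does not say so, and 6.1 no. 1c points the other way.

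A reader might also infer that patients with gross residual tumor (R2) are counted as disease-free from surgery. R2 is a foreseen outcome in 3.2 no. 2, and neither 11.4.2, "Defined as the duration of time from surgical resection of the primary tumor until local recurrence or death, whichever occurs first", nor 11.4.4 sets a margin condition. But the protocol is silent on these patients; it does not state that they count as disease-free. Section 7.5 calls for re-resection of positive soft-tissue margins where possible, and it says of unresectable tumors: "Unresectable tumors may be palliated with surgery, chemotherapy, or additional radiation therapy. These patients will be taken off protocol". It does not equate R2 with unresectable, so some cases may remain. Regrowth in such a patient could be recorded as local recurrence. Exclusion, restriction to R0/R1 resections and an event at surgery are all defensible choices, and the choice is commonly left to the analysis plan.

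**Conclusion.** The point holds for DFS. Section 11.4.4 does not count an isolated regional recurrence, 6.1 no. 1c treats regional disease as distinct from distant disease, and 10.4.3 does not collect it. Under the literal rule DFS can be overstated and cannot be understated. Under the assumptions above, the upper limit is 2.9 points (n = 35) to 4.0 points (n = 25) per affected patient, and the effect is zero if no patient has such a failure.

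A reader might infer more than the documents support:

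- **That DFS is in fact overstated.** No nodal recurrence rate is given, so only the direction is known.
- **That local control is overstated too.** Time to local recurrence and local DFS count local failure by design, and distant DFS counts distant failure by design. Leaving regional disease out of them is no defect.
- **That the bias could reach 16 points.** That would need four affected patients among 25 (4/25), for example two nodal and two R2, all assumed and none with a later counted event.

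The primary endpoint and the sample size are unaffected. How R2 patients are handled is a choice for the analysis plan and not a shown error.

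**What to change.** - **11.4.4:** list the events as local, regional or distant recurrence, or death.
- **10.4.3:** add regional recurrence to the items monitored, so that the event is recorded.
- **11.4.5:** name regional recurrence in PFS as well. This is for consistency, since a new lesion may already count there as progressive disease.

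The cost is a wording change in two definitions, one more item on the follow-up report, and possibly a slightly less favourable DFS estimate. Nothing changes in the primary analysis or in accrual.
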